#### Timeline

Participants will be enrolled for a total of 24 months, with study follow-up visits at months 4, 8, 12, 18, and 24 (Fig. 1). The intervention components will be applied for the first 12 months of enrollment.

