#### Outcome measures

We will be collecting data using viral load results (at month 4 and month 12—obtained from patient records and the National Health Laboratory Service online system), EAMs (daily), pharmacy refills (monthly), and participant and staff surveys. The primary outcome will be viral suppression at month 24 post-enrollment as measured by plasma HIV-1 viral load <50 copies/mL. Secondary outcomes will include viral suppression at month 12, change in viral load over time, and total days of unsuppressed virus during study participation. Additional secondary outcomes include the following: mean electronic adherence and percent of participants ≥90% and ≥80% adherence in months 12 and 24; mean adherence over months 1–12 and 1–24; retention in ART care (percent of participants attending all refill visits within 7 days for monthly refills and 14 days for longer refill intervals) over months 1–12 and 1–24; percent of participants attending ≥75% refill visits (within 7 days), over months 1–12 and 1–24; percent of participants lost to care, defined as no clinic contact for ≥12 weeks at month 24); and time to suboptimal adherence detection and linkage to support (number of days from month 0 to day identified as nonadherent, as per the definition used in their intervention; number of days from month 0 to linkage to ROTF support).

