#### Randomization

We will randomly assign 512 participants representing three clinics to one of 16 study conditions (Table 2) using a permutation allowing for the study conditions to include an equal number of participants, which is 32 (16*32 = 512). We developed the random assignment of participants in Stata v.14 using *runiform* and *rank* functions. The randomization sequence is concealed from all study staff involved in recruitment, enrollment, and randomization. Once eligibility has been determined, designated study staff will randomly assign participants to a study condition, using the REDCap electronic database.

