To estimate treatment effects, we will adopt an ITT analytic approach and all 512 participants will be analyzed according to their randomized condition. The primary outcome is viral suppression at 24 months (see Table 1), measured as a binary variable, to allow us to assess a sustained post-intervention effect [64]. We will use logistic regression to estimate main and interaction effects on the odds of viral suppression. We will use an exchangeable correlation matrix, accounting for clustering by health facility for all analyses. Participants’ receipt of intervention components will be effect-coded. That is, following Kugler et al., [65] we will code participants’ receipt of an intervention component as 1, and nonreceipt as −1. To estimate the main effect of an intervention component, we will multiply the coefficient term by two and exponentiate it (i.e., implementing the mathematical operation as follows: Exp(2*coefficient term)). We will use the same approach to estimate interaction effects between components. Similarly, we will use logistic regression to estimate effects of components on secondary outcomes measured as a binary outcome (viral load at month 12; adherence; retention). We will use linear or Poisson regression to estimate effects of components on outcomes measured as a continuous variable (e.g., mean change in viral load from month 0 to 12 and month 0 to 24) or count variable (e.g., days of unsuppressed virus), respectively. We will compare dropout rates and characteristics of participants who drop out or are lost to follow-up with those retained to assess potential for bias. We will also assess evidence of contamination by examining data from our detailed REDCap records and texting logs, using any such evidence when interpreting data on outcomes. Moderating effects will be explored through regression modeling following Hayes [66]; mediators will be assessed using the approach by Valeri and VanderWeele, which allows for logistic modeling, and sensitivity analyses will be conducted on key assumptions per Imai [67, 68]. For all quantitative analyses, we adopted REDCap for data capture and SAS for data analysis [69].

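### Poisson regression is assigned to total days of unsuppressed virus with no dispersion parameter or participant-level variance; two of the three variance choices it leaves open give standard errors that are too small

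*Protocol article*

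**What the plan says.** In the protocol article, Outcome measures lists as a secondary outcome "total days of unsuppressed virus during study participation". Timeline fixes the length of participation: "Participants will be enrolled for a total of 24 months".

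Data and statistical analysis then assigns the models. "We will use linear or Poisson regression to estimate effects of components" covers continuous and count outcomes in turn, and the count example is "or count variable (e.g., days of unsuppressed virus), respectively". The same paragraph adds "We will use an exchangeable correlation matrix, accounting for clustering by health facility for all analyses". The analysis set is complete by design: "all 512 participants will be analyzed according to their randomized condition". Randomization confirms the number of clusters: "We will randomly assign 512 participants representing three clinics to one of 16 study conditions".

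The article does not say whether standard errors are model-based or sandwich, or whether the Poisson scale is fixed at 1 or estimated. It offers no alternative model for overdispersion.

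**The concern.** Days of unsuppressed virus are not a count of independent events. Each participant contributes one duration, bounded by follow-up and built from a small number of viral load tests. Some people suppress early and some stay unsuppressed for many months, so totals will differ between people by far more than the square root of the mean, which is all that a Poisson model with scale 1 allows.

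A Poisson mean model remains a reasonable way to estimate a ratio of mean days. What is at risk is the standard error. The article's first aim judges the five components on primary and secondary outcomes, and the Cost-effectiveness analysis section carries forward the components found efficacious. Error bars that are too narrow on this outcome could help promote or drop a component on noise.

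**Working it through.** The article states no figure for this outcome, so there is nothing to reproduce. The check asks how far the standard error is off under each variance choice that the text leaves open.

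**Inputs from the article.** Follow-up of 24 months, about 730 days; 512 participants in 16 conditions of 32, hence 256 against 256 for each main effect; three clinics; 51–86% suppressed at 12 months (Background).

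**Inputs assumed.** The mean, SD and shape of the outcome.

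**Step 1: what scale 1 requires.** Poisson with scale 1 needs SD = √mean. At a mean of 150 days that is √150 ≈ 12 days; at 272 days it is √272 ≈ 16 days.

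**Step 2: shortfall with scale 1.** The standard error is too small by k = √(variance/mean). For large samples the type I error at a cut-off of 1.96 is about 2 × [1 − Φ(1.96/k)].

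| Assumed distribution | Variance/mean | k | Approximate type I error |
|---|---|---|---|
| Mixture, mean 272, SD 245 (60% about 110 days, 20% uniform 120–480, 20% at 730) | 245²/272 ≈ 221 | 14.9 | 90% |
| Gamma, mean 150, SD 94 | 94²/150 ≈ 59 | 7.7 | 80% |
| Unimodal, deliberately favourable, mean 110, SD 40 | 40²/110 ≈ 14.5 | 3.8 | 61% |

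Two-point distributions with a share p suppressed at *a* days and the rest at *b* days have mean pa + (1−p)b and variance p(1−p)(b−a)². With p = 0.86:

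- 0 and 730 days: mean 102.2, variance 64,161, k = √627.8 ≈ 25.
- 120 and 365 days: mean 154.3, variance 7,227, k = √46.8 ≈ 6.8.

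Over all the distributions tried, k runs from about 4 to about 25. At k = 25 the formula gives a type I error of about 94%.

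**Step 3: simulation of the design.** There were 600 null trials of the 16-condition design with 512 participants in three clinics. About 67% were suppressed, with totals uniform on 30–120 days; the rest were uniform on 365–730 days. The empirical SD of a main-effect coefficient was 0.0435.

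| Analysis | Mean SE | Empirical SD / mean SE | Type I error |
|---|---|---|---|
| Poisson, scale 1 | 0.0029 | 14.9 | 88% |
| Exchangeable Poisson GEE by clinic, model-based, scale 1 | 0.0029 | 15.0 | 89% |
| Exchangeable Poisson GEE, sandwich over three clinics | 0.0318 | 1.37 | 25% |
| Poisson, Pearson scale (quasi-Poisson) | 0.0443 | 0.98 | 4.0% |
| Poisson, participant-level robust SE | 0.0441 | 0.99 | 4.3% |

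**Step 4: the three distributions of Step 2, simulated.** With 300 null trials each and no true clinic effect:

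| Distribution | Scale 1 | Clinic sandwich | Quasi-Poisson | Participant-level robust |
|---|---|---|---|---|
| Mean 272, SD 245 | 90% | 25% | 4.5% | 4.6% |
| Mean 150, SD 94 | 79% | 25% | 5.1% | 5.2% |
| Mean 110, SD 40 | 60% | 24% | 5.6% | 5.7% |

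The scale-1 column agrees with the formula in Step 2. The sandwich column hardly moves while the dispersion changes about 15-fold (14.5 to 221), so its excess does not come from overdispersion. It comes from estimating a variance from three clusters: the sandwich has rank at most three, while the model has at least six coefficients before any interaction. A constant shortfall of 1.37 would by itself give about 15%; the remainder is consistent with a standard error from three clusters being highly variable.

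**Step 5: the third reading.** An exchangeable GEE with model-based errors and a moment-estimated dispersion was run on the first two distributions (400 null trials each). The ratios were 1.02 and 1.01, with type I error of 5.6% in both.

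**The case against.** The strongest reply is that the article does not specify a plain Poisson regression. The exchangeable-correlation sentence covers all analyses, so the stated model is a clustered, GEE-type Poisson, and nothing in the text fixes the scale at 1. With a dispersion estimated from the data and model-based errors, that model is close to nominal (Step 5). With sandwich errors the variance assumption no longer sets the standard error, and what remains is a three-clinic problem that would be expected with any outcome type. The distributions are assumed, the outcome is secondary, and a condensed article may leave the variance estimator to the analysis plan.

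Most of this stands, and it limits the point. A reader might infer that the planned standard errors will be about 8 to 15 times too small, that the outcome is known to be bimodal, or that nearly every component will look significant by chance. The article supports none of these. The large shortfalls hold only if the scale is fixed at 1, the shape of the outcome is not given, and how the rule counting missing viral loads as detectable enters a day total is not stated.

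What does not stand is that the clustering sentence settles the matter. Clinic-level correlation leaves both the scale-1 and the clinic-sandwich reading open, and both give wrong error bars. Naming a model family whose default variance does not suit the chosen example is a stated choice, and so more than a missing detail.

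**Conclusion.** The point holds in conditional form, for one secondary outcome. Poisson regression with exchangeable correlation by clinic is assigned to a bounded per-person total of days, and nothing stated protects the standard errors from overdispersion. Under the assumed distributions:

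- with scale fixed at 1, standard errors are roughly 4 to 25 times too small, and type I error was about 60% to 90% where simulated;
- with a sandwich over three clinics, they are about 1.4 times too small, and type I error is about 25%, which is a consequence of three clusters;
- with an estimated scale or participant-level robust errors, type I error is about 5%.

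The direction does not depend on bimodality, since the favourable unimodal case also fails with scale 1. The sizes do depend on the assumed distributions. The primary outcome is not affected by the overdispersion issue.

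**What to change.** In Data and statistical analysis, state that total days of unsuppressed virus will be analysed with a log-link mean model, clinic as a fixed factor, and either an estimated scale (quasi-Poisson) or participant-level robust standard errors. An acceptable alternative is linear regression of days with participant-level robust standard errors and clinic as a fixed factor, which reports the effect directly in days. State also that the Poisson scale will not be fixed at 1 and that standard errors will not rest on a sandwich over three clinics.

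The cost is one sentence of analysis wording. It needs no new data and no change to the design or the sample size.

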#### Cost-effectiveness analysis

We will identify the intervention components shown to be efficacious, taking main effect sizes and interactions into account. Estimates on durability of effect will be conservative for the main analyses (e.g., we will assume the same effect over 24 months as observed in the study). The main cost-effectiveness analyses will assume a payer perspective and a 3% discount rate. Sensitivity analyses will explore the impact of uncertainty on key variables, varying the probability distributions of each factor as well as the time horizon. We will consider 5-year and 10-year time horizons, as well as different perspectives (payer and societal) and examine the effect of different discount rates (0%, 5%). Further, we will undertake cost-effectiveness analyses guided by the Proctor framework [52]. Thus, we will determine an adjusted CE outcome (AdCE) for each intervention component as a function of CE plus implementation and client outcomes defined in Aim 2. We will apply utility levels obtained from key stakeholders, incorporating the value they attach to each implementation outcome, and calculate AdCEs using the following equation:$$AdCE = CE / ({IO}_{1}{U}_{1} + \dots + {IO}_{8}{U}_{8})$$where CE = cost-effectiveness, IO is the success score of specific outcomes, and U is the utility of each outcome. Utilities will be expressed dichotomously (high value = 1; low value = 0) for simplicity and clarity. Thus, a given CE outcome may be more (or less) valued in the context of higher (or lower) implementation outcomes (e.g., acceptability and adoption), all other factors being similar. After the modeling exercises, members of the core team will identify the options that best combine a positive effect, low cost, and implementation priorities, including staff time required, eliminating poorly performing and costly elements.

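### The adjusted cost-effectiveness index works against its own stated aim when a component's cost-effectiveness ratio is negative

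*Protocol article*

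**What the plan says.** The Cost-effectiveness analysis section of the protocol article first selects the components found to be efficacious. It then describes the main analysis (payer perspective, 3% discount rate) and the sensitivity analyses, which include 5- and 10-year horizons and a societal perspective. After that it adds a supplementary index: "we will determine an adjusted CE outcome (AdCE) for each intervention component as a function of CE plus implementation and client outcomes".

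The printed formula, in plain notation, is AdCE = CE / (IO1 x U1 + ... + IO8 x U8), "where CE = cost-effectiveness, IO is the success score of specific outcomes, and U is the utility of each outcome". On the source of the utilities it says: "We will apply utility levels obtained from key stakeholders, incorporating the value they attach to each implementation outcome". On their values: "Utilities will be expressed dichotomously (high value = 1; low value = 0) for simplicity and clarity".

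The purpose is stated too. Other things being similar, "a given CE outcome may be more (or less) valued in the context of higher (or lower) implementation outcomes". Once the modelling is done, "members of the core team will identify the options that best combine a positive effect, low cost, and implementation priorities".

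The article does not say whether CE is a ratio or in which direction it is better, gives no range for IO, and gives no rule for a negative CE.

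**The concern.** The formula and its aim stand in the same paragraph, so one can be tested against the other without the fuller protocol. Dividing by a larger number moves any value towards zero. For a positive cost per outcome that is an improvement, as intended. For a negative one, which for an effective component means that it saves money, it is a deterioration. The index would then penalise good implementation among the components a payer would most want to keep.

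At stake is Aim 3 in the Optimization phase section: modelling a package optimised jointly for cost-effectiveness and implementation success. AdCE is the only numerical rule in the article that joins the two.

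A second, smaller question is whether AdCE can be read on the same scale as CE, since its denominator is a raw sum of up to eight terms.

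**Working it through.** The article reports no AdCE value, so there is no figure to reproduce. The formula, the 0/1 utilities and the limit of eight outcomes come from the article. The CE values and IO scores below are assumed for illustration. Write S for the sum of IO x U, and read CE as cost per unit of effect, lower being better.

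**1. Equal CE, different implementation**

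| CE | S = 6 (better implemented) | S = 3 (worse implemented) | Looks better |
|---|---|---|---|
| +200 | 200/6 = 33.3 | 200/3 = 66.7 | better implemented, as intended |
| -200 | -200/6 = -33.3 | -200/3 = -66.7 | worse implemented, against the aim |

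**2. Unequal negative CE.** Let A have the more negative CE and the larger S. A stays ahead only if |CE_A| / |CE_B| exceeds S_A / S_B. With eight valued outcomes and IO on 0-1:

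- A: CE = -1000, IO 0.8, S = 8 x 0.8 = 6.4, AdCE = -1000/6.4 = -156.25.
- B: CE = -600, IO 0.3, S = 8 x 0.3 = 2.4, AdCE = -600/2.4 = -250. Here 1000/600 = 1.67 is below 6.4/2.4 = 2.67, so the order reverses.
- B: CE = -400, IO 0.6, S = 8 x 0.6 = 4.8, AdCE = -400/4.8 = -83.3. Here 1000/400 = 2.5 exceeds 6.4/4.8 = 1.33, so the order is kept.

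**3. The opposite reading of CE.** If CE were effect per unit cost or net benefit (higher is better), dividing by a larger S would lower a positive value and so penalise good implementation. Cost per effect is therefore the reading that suits the formula best, and under it the formula meets its aim only for positive CE.

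**4. Scale.** Take CE = 1000 and every IO = 0.8, and vary only the number of outcomes rated high value:

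| Outcomes with U = 1 | S | AdCE |
|---|---|---|
| 1 | 0.8 | 1250 |
| 2 | 1.6 | 625 |
| 4 | 3.2 | 312.5 |
| 8 | 6.4 | 156.25 |

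Implementation is identical throughout, yet AdCE varies eight-fold (1250/156.25 = 8). AdCE is below CE when S exceeds 1 and above it when S is less than 1. With all utilities 0, S = 0 and AdCE is undefined.

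**5. What normalising does.** Replace S by the weighted mean S / sum(U), with IO on 0-1.

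- CE = 4000, eight valued outcomes, S = 6: the printed formula gives 4000/6 = 667. The weighted mean is 6/8 = 0.75, which gives 4000/0.75 = 5333. At a mean of 1, AdCE equals CE.
- With one set of utilities common to all components, every denominator is divided by the same sum(U), so the ranking of positive ratios cannot change.
- The sign problem remains. CE = -1000 gives -1000/0.4 = -2500 at mean IO 0.4 and -1000/0.8 = -1250 at 0.8, so the worse-implemented component still looks better.

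**The case against.** The strongest defence is that a negative CE is an edge case. The Costing section lists only set-up and delivery costs, all positive, and does not mention averted care costs. The 5- and 10-year horizons, where savings are most plausible, are sensitivity analyses, and the text does not tie AdCE to them. The main analysis takes the effect observed over 24 months. AdCE is also supplementary: the core team weighs effect, cost, implementation priorities and staff time, and would see a negative CE. Finally, this is a condensed article, and the scoring of IO and the exact CE measure may well be set out in the full protocol.

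Most of that stands, and it limits how far the point reaches. It does not remove the point, because the formula and its aim are both printed and they disagree for negative CE. That is a stated rule that can mislead, not a missing detail.

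A reader might infer more than the documents support:

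- That the formula reverses the ranking of cost-saving components in general. It does so with certainty only when their CE values are equal; otherwise the order may hold.
- That harmful components would pass as cost-saving ones. A negative ratio alone cannot separate them, but the section starts from components shown to be efficacious and ends by requiring a positive effect, which largely screens them out.
- That positive ratios always look cheaper than they are. This needs S above 1 on a score scale the article does not give. With one valued outcome and IO 0.4, a CE of 1000 becomes 1000/0.4 = 2500.
- That the raw sum distorts a threshold decision. The article states no threshold, and the unadjusted CE remains available.

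**Conclusion.** The concern holds in a limited form. If CE is a cost per effect with lower better, the adjustment serves its stated aim only for positive CE. Of two components with the same negative CE, the worse-implemented one gets the more favourable AdCE; in the illustration it looks twice as good (-66.7 against -33.3). With unequal CE, reversal depends on whether the ratio of the CE values falls below the ratio of the implementation sums. Whether any component will have a negative CE cannot be told from the article, which neither predicts nor excludes it.

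The lack of normalisation is secondary. It makes the size of AdCE depend on how many outcomes are rated high value, so AdCE cannot be read as a cost per outcome. It does not alter the ranking of positive ratios when the utilities are common to all components, which is assumed here because the article does not say that they differ.

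The practical weight is small: a worthwhile tidy-up of a supplementary index.

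**What to change.** In the Cost-effectiveness analysis section:

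1. State that CE is a cost per unit of effect with lower better, if that is meant.
2. Report any component with a negative ratio separately, before adjustment, as dominant (cost-saving and effective) or dominated (more costly and less effective), with its implementation scores alongside. Apply the AdCE formula only to positive ratios. This step is what cures the sign problem.
3. For readability, scale IO from 0 to 1 and divide CE by the weighted mean, sum(IO x U) / sum(U). AdCE then equals CE at perfect implementation and is never below it. This needs at least one utility equal to 1, because with all utilities 0 the mean is 0/0; say what will be reported in that case.

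The cost is a line or two of text. No new data are needed, the ranking of positive ratios is unchanged under common utilities, and the trial's design and efficacy analyses are untouched.

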#### Ethics approval

This study received ethical approval from the Boston University Institutional Review Board (IRB No: H-41920) on 14 September 2021 and the University of Cape Town Human Research Ethics Committee (HREC Ref: 568/2021) on 10 November 2021.

A trial management committee consisting of the principal investigators, key co-investigators, and site operations managers meets on a monthly basis to discuss study progress, monitoring, and operations.

We will convene an independent Data Safety Monitoring Board (DSMB) for this study comprised of individuals with topic and region expertise matching the study characteristics . The DSMB will periodically review cumulative study data to independently evaluate safety, study conduct, scientific validity, and data integrity of the study. The DSMB will assess interim results 12 months after 50% of the sample has been enrolled to independently determine study continuation. While no medical adverse events are expected in this study, there is the potential for social or mental harms. These will be collected spontaneously, reviewed by the trial management committee, and reported to both the DSMB and ethics committee.

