S2: Peer support (Basic or enhanced)	Adherence support	Monthly for 3 months once suboptimal adherence detected	Basic: One-on-one or group adherence sessions delivered by clinic counsellors Enhanced: One-on-one motivational interviewing delivered by study staff

Abbreviations: *SoC*, standard of care; *VL*, viral load; *ART*, antiretroviral therapy

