#### Intervention components

At enrollment, each participant will be issued an EAM to measure adherence over time, and for those assigned to M3, to actively monitor adherence. Enrolled participants will be randomized to one of 16 study conditions (i.e., combination of monitoring and intervention strategy—see Table 2). Four of the five intervention components (M1, M2, M3, & S1) can either be switched “on” (the component is applied) or switched “off” (the component is not applied). The counselling component (S2) can be either basic (standard of care) or enhanced (motivational interviewing). As this study includes only behavioral interventions, all routine medical care provided by the clinics will continue as needed. There is no prohibited concomitant care. While the study interventions monitor and promote adherence and retention in care, there are no additional measures to promote retention within the study itself (e.g., outreach to participants who have missed study visits), as these additional activities would influence retention in care as an outcome and undermine the assessment of our interventions.

**Table 2 Tab2:** Intervention components and study conditions in the fractional factorial design

**Study condition** **Intervention components**	1	2	3	4	5	6	7	8	9	10	11	12	13	14	15	16
Core (standard care): After a VL test shows unsuppressed virus, the patient is alerted at the next clinic visit and given a counselling session	X	X	X	X	X	X	X	X	X	X	X	X	X	X	X	X
M1. Call to the patient after VL test result of unsuppressed virus (M1/Call)	O	O	O	O	O	O	O	O	X	X	X	X	X	X	X	X
M2. Pharmacy refill monitoring + Call to the patient (M2/PRM)	O	O	O	O	X	X	X	X	O	O	O	O	X	X	X	X
M3. Electronic adherence monitoring + Call to the patient (M3/EAM)	O	O	X	X	O	O	X	X	O	O	X	X	O	O	X	X
S1. Weekly check-in text messages (S1/Text)	O	X	O	X	O	X	O	X	O	X	O	X	O	X	O	X
S2. Peer support counselling: Basic (B) or Enhanced (E) (S2/Peer)	E	B	B	E	B	E	E	B	B	E	E	B	E	B	B	E

Abbreviations: *VL*, viral load; *PRM*, pharmacy refill monitoring; *EAM*, electronic adherence monitoring

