#### Mediator and moderator variables

Annual surveys will allow us to collect data on SDT constructs (such as autonomy support, motivation, perceived self-competence, social support, and ART knowledge) to test the effect on each in mediating the association between the intervention and outcomes. Further, we will collect data on substance use, depression, gender inequity, stigma, and transport or clinic-related issues to test the extent to which each of these variables independently or in combination moderate the association between the intervention and outcomes.

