#### Blinding

This is an unblinded study as the study condition to which each participant has been assigned can be deduced by looking at the interventions that they have received. We considered conducting a blinded analysis. However, since all the information to unblind the assigned groups would be required, we determined that there was no way of practically conducting a blinded analysis and determined that all the analyses will be unblinded.

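### Social and mental harms are collected only as spontaneous reports, which can under-count them and can skew any reading of harm counts by component

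*Protocol article*

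**What the plan says.** The Ethics approval section identifies the risk: "While no medical adverse events are expected in this study, there is the potential for social or mental harms". It then fixes the method of capture: "These will be collected spontaneously, reviewed by the trial management committee, and reported to both the DSMB and ethics committee". The reports have a use, since the same section states: "The DSMB will periodically review cumulative study data to independently evaluate safety, study conduct, scientific validity, and data integrity of the study". It also gives the DSMB an interim assessment of whether the study continues.

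The Blinding section states: "This is an unblinded study as the study condition to which each participant has been assigned can be deduced". It adds that the analyses will be unblinded too.

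Contact with study staff depends on assignment. Table 1 gives phone calls under M1, M2 and M3, and 12 weekly automated texts with an option to reply under S1. For S2 it gives "Enhanced: One-on-one motivational interviewing delivered by study staff", whereas basic sessions are given by clinic counsellors. Some contact is common to all: the Timeline section schedules everyone "with study follow-up visits at months 4, 8, 12, 18, and 24".

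Under Mediator and moderator variables, "we will collect data on substance use, depression, gender inequity, stigma" appears as part of the moderator data. No link to harm reporting is stated.

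**The concern.** A spontaneous report needs two things: a participant willing to raise the matter, and a person in the study's reporting line to raise it with. Here the second is partly randomised. A participant who receives calls, or motivational interviewing from study staff, has more occasions to mention an unwanted disclosure or distress than one whose counselling comes from clinic staff. Because staff know the assignment, it can also influence whether a remark is recorded as a harm.

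Two things are at stake. The first is under-counting: the DSMB judges safety from reports that nobody was asked for. The second is unequal under-counting: if the DSMB looks at harms by component, a component with more contact can appear worse, and harm under a component with less contact can go unseen. No later analysis can recover harms that were never asked about.

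**Working it through.** The document gives no harm rate, no reporting probability and no harm comparison, so there is no figure to reproduce. The check is whether contact really differs by assignment, and how much distortion that could cause under stated assumptions.

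**Step 1. Contact by assignment (Table 2 and Randomization).** Each component is on (or enhanced) in 8 of 16 conditions. At 32 per condition, that is 8 × 32 = 256 against 256. Five conditions have one component on, ten have three and one has five. Potential contact differs by assignment, but no condition has no active component.

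**Step 2. What limits the difference.** M3 data are reviewed weekly, but a call follows only if doses are missed. S1 and S2 start only once suboptimal adherence is detected. Components are applied for the first 12 months of the 24. All participants have five study visits, and the consent document gives them study staff contact details.

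**Step 3. Illustration with equal true harm.** Let *q* be the assumed chance that a harm is volunteered at any one contact, with five shared visits and *k* extra contacts.

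- Share reported with visits only: 1 − (1 − q)^5. For q = 0.05, 0.10, 0.20 and 0.40 this is 23%, 41%, 67% and 92%.
- Observed ratio if everyone assigned gets the extra contacts: R = [1 − (1 − q)^(5+k)] / [1 − (1 − q)^5].
- Observed ratio if only a fraction *t* is triggered, independently of harm: 1 + t(R − 1).

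Example, q = 0.10 and k = 3: R = (1 − 0.9^8)/(1 − 0.9^5) = 0.5695/0.4095 = 1.39. With t = 0.3: 1 + 0.3 × 0.39 = 1.12.

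| q | k = 3, all | k = 3, t = 0.5 | k = 3, t = 0.3 | k = 6, all | k = 6, t = 0.5 | k = 6, t = 0.3 |
|---|---|---|---|---|---|---|
| 0.05 | 1.49 | 1.24 | 1.15 | 1.91 | 1.45 | 1.27 |
| 0.10 | 1.39 | 1.20 | 1.12 | 1.68 | 1.34 | 1.20 |
| 0.20 | 1.24 | 1.12 | 1.07 | 1.36 | 1.18 | 1.11 |
| 0.40 | 1.07 | 1.03 | 1.02 | 1.08 | 1.04 | 1.02 |

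All values of q, k and t are assumptions. The model leaves out effects in both directions. Contact from the other components is balanced across the two levels, which pulls the ratio towards 1. Harms that arise late have fewer visits left, and harms may cluster in people whose adherence triggers contact; both push it up.

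The pattern does not depend on the exact inputs: under-counting and distortion are both greatest when volunteering is rare, and both shrink as the shared visits capture more.

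**The case against.** The strongest reply is that no stated decision rests on a harm comparison. Harms are not among the outcomes, no between-component test of harms is described, and reports simply go to the trial management committee, the DSMB and the ethics committee. This stands: the point concerns monitoring and interpretation, not a planned analysis.

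The contact gap is also smaller than Table 1 suggests at first sight, for the reasons in step 2 of the check. This stands too, and it limits the size of the bias.

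Depression and stigma data are collected in any case. The article does not say that they serve only as moderators, and the DSMB may review cumulative study data. But nothing ties these measures to harm reporting, and they do not ask whether the study caused a problem.

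Finally, the visit schedule figure and the full protocol are not shown, so the content of the visit forms cannot be checked. What can be said is that the article states the collection method, and that the method is spontaneous.

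A reader might also infer that the bias carries into the choice of acceptable components. The document does not support that. The Implementation outcomes section measures acceptability by questionnaires given to all enrolled patients and by interviews, and the Cost-effectiveness analysis section does not name spontaneous harm counts as an input to the package.

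**Conclusion.** The point holds as a weakness in a stated method. Spontaneous capture in an unblinded trial with unequal staff contact can under-count the one kind of harm that the trial expects, and can bias any reading of harm counts by component. The size cannot be quantified from the document. The illustrated ratios run from near 1 to 1.91, and the upper end needs rare volunteering plus six extra contacts for everyone assigned.

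Two stronger readings are tempting and should be resisted:

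- That harm counts would follow contact instead of harm. Counts are true harm multiplied by the chance of reporting, and the common visits and contact details give every condition a route to report.
- That a spurious doubling is to be expected. With an assumed 6% true harm, 256 × 0.06 = 15.4 harms per level; 80% reporting with extra contact and 40% without would show about 12 against 6. That requires everyone in the on half to receive the extra contact. If 30% do, it is 15.4 × (0.3 × 0.8 + 0.7 × 0.4) = 8.0 against 6.1.

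The primary outcome, sample size and efficacy analysis are untouched. This is a cheap improvement to safety monitoring.

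**What to change.** At each existing study visit (months 4, 8, 12, 18 and 24), ask every participant in all 16 conditions the same short set of questions on social and mental harm. Continue to accept spontaneous reports, but record them separately. Report both to the DSMB by component level, alongside the depression and stigma survey data already collected, and base any between-component reading on the solicited data.

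The cost is a few questions on existing REDCap forms, a few minutes per visit and one table in the DSMB report. More minor harms will be recorded. One gap remains: the Intervention components section says "there are no additional measures to promote retention within the study itself", so harms in participants who stop attending visits would still be missed. The DSMB table should say so.
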